### Phase 3: Trial Intervention

#### Trial Design

We will employ a matched, randomized pilot study design in 2 government hospitals with comparable resources, patient volume, and basic patient characteristics. One hospital will be randomized to receive the HITSystem 2.0 intervention and the other hospital will maintain standard of care PMTCT services. An extended 18-month implementation period will allow 9 months to reach the sample size requirement of n=54 at each hospital and another 9 months to ensure complete prospective outcome data from the first PMTCT appointment in pregnancy until the infant’s first HIV DNA PCR test result is determined. This follow-up period will assess complete retention throughout PMTCT services, ART adherence, and rates of infant HIV transmission. We will also collect retrospective PMTCT outcome data from each hospital for the 18 months before implementation to facilitate pre- and postcomparisons at the same facility.

Satisfaction interviews with HITSystem 2.0 users (HIV positive women and providers) will inform barriers to use that can be targeted either through future strategic refinement of the design or collaboration with key partners to address constraints beyond the scope of this intervention.

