*PMTCT service utilization* will be documented in the patient file and relevant PMTCT-related facility registers (intervention and control) as required by the Kenyan Ministry of Health. At the intervention hospital, a new record will be created in the HITSystem 2.0 during PMTCT enrollment and will be updated at each subsequent visit, including mobile phone number(s) and residence tracing information. Prospective clinical data from the mother-infant pair will be captured in the HITSystem 2.0 to track medication adherence, appointment attendance, delivery outcomes, and postpartum infant prophylaxis data, automating provider alerts and SMS text messages to participants as indicated. Any information that is not captured in the HITSystem at the time of the patient’s visit (owing to workflow, connectivity, or other challenges) will be updated as soon as possible after the visit, referencing any relevant paper-based patient and facility records needed. All relevant data to measure the targeted PMTCT outcomes will be entered and maintained in the HITSystem 2.0.

At the control site, paper-based patient files and facility registries are the primary record-keeping source for PMTCT data. A study staff member will visit the control site quarterly to review clinical records to document and update PMTCT services received by women enrolled in the study. Multiple sources will be cross-referenced to collect standard of care data at the control hospital: (1) pregnant women/mothers’ medical records, (2) hospital ANC registry book, (3) pharmacy ART registry, (4) maternity registry, and (5) HIV-exposed infant registry.

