#### Medication Adherence

As VL is still not consistently collected during pregnancy, we will rely on other indicators of adherence including self-report of missed doses in the 7 days before appointment (prescribed vs taken) and pill counts conducted by relevant providers (dispensed vs returned). Adherence data will be entered in the HITSystem 2.0 at each appointment. We will calculate the proportion of patients who report >95% adherence to doses prescribed (7-day self-report) and pill count.

*Hospital delivery* will be estimated from the proportion of pregnant mothers who deliver at a health facility. Women who do not deliver at the study hospital will be contacted within 2 weeks of their estimated due date to check on their progress, document location of birth, and encourage prompt return to the facility for postpartum and postnatal care. *EID enrollment* will be measured using the proportion of HIV-exposed infants tested by 6 weeks of age (<7 weeks).

*Infant and maternal mortality* will be reported separately, noting all available data on date and cause of death. A future study will utilize a design with a longer follow-up period and larger sample size to adequately evaluate perinatal transmission of HIV.

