## Discussion

Previous HITSystem pilot data and studies have demonstrated significant success in improvement of EID outcomes particularly in improving the efficiency and quality of key EID outcomes [32-34,38]. Leveraging the improved linkage of health facilities, mother-infant pairs, and laboratories in the context of EID, the HITSystem 2.0 (PMTCT) will expand the current Web-based platform to bridge the gap between maternal and pediatric HIV services. Outcomes at each step of the PMTCT cascade will be analyzed, and specific challenges will be identified.

This study will design and implement the HITSystem 2.0 through formative qualitative research, intervention development using the 4Ds process, and a pilot implementation period as described above. It will also provide user satisfaction data by highlighting the HITSystem 2.0’s usefulness, acceptability, challenges, and recommendations to improve the intervention. The proposed HITSystem 2.0 will integrate maternal and infant HIV services in one system-level, Web-based intervention that will provide linked, prospective data for mother-infant pairs, which has been identified as a problematic gap in the current system. The findings of this study will refine the HITSystem 2.0 intervention, particularly tracking and utilization of challenging measures such as medication adherence and antenatal VL results to enhance system performance and implementation strategies in a larger scale efficacy trial.

Although this intervention will focus on health system improvement to enhance quality of care for women and infants in the facility setting, the study will not directly target PMTCT uptake, which would require community-based outreach. Given that intervention site data will be tracked via the HITSystem whereas control site data will be captured via disparate paper-based registries and patient files, there may be discrepancies in data quality and documentation of services rendered between control and intervention sites; all efforts will be made to capture any available data at control sites to minimize this limitation. As the study design and implementation evolve, we anticipate that eHealth technologies in the study regions will likewise evolve and influence the standard of PMTCT care. These external factors will be documented and accounted for in the design and analyses.

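### The same-facility pre/post comparison crosses a change in outcome ascertainment when HITSystem 2.0 goes live, so better recording can pass for better retention

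*Protocol article*

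**What the plan says.** Trial Design commits to collecting "retrospective PMTCT outcome data from each hospital for the 18 months before implementation to facilitate pre- and postcomparisons at the same facility". It does not say which records will supply the earlier period or by what rule. Statistical Analyses describes no pre/post analysis.

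For the later period at the intervention hospital the source is fixed. In the PMTCT service utilization paragraph under Procedures, "a new record will be created in the HITSystem 2.0 during PMTCT enrollment" and it is updated at each visit. Gaps are filled later from paper records, and "All relevant data to measure the targeted PMTCT outcomes will be entered and maintained in the HITSystem 2.0". The training paragraph adds an on-site research assistant who supports timely entry and a remote team that reviews entries. Fidelity Assurance Procedures adds routine review of entries for completeness.

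The hospital-delivery paragraph, under Medication Adherence, adds: "Women who do not deliver at the study hospital will be contacted within 2 weeks of their estimated due date". That contact records where the birth took place and also encourages return to care. It is not limited to one hospital.

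The Primary Outcome section makes complete retention all-or-nothing: ART started, all scheduled appointments attended, hospital delivery, and infant PCR before 7 weeks. The Discussion says HITSystem 2.0 will supply "linked, prospective data for mother-infant pairs, which has been identified as a problematic gap in the current system". It acknowledges unequal documentation between the control and intervention sites, but not between periods.

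**The concern.** HITSystem 2.0 is built in Phase 2, so neither its records nor the due-date contact can exist for a retrospective period. Under an all-or-nothing outcome, one unrecorded visit, unseen delivery or unlinked infant test turns a truly complete mother-infant pair into an incomplete one. If capture improves at go-live, measured retention at the intervention hospital rises even if care is unchanged.

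This matters because there is one hospital per arm, so arm and hospital coincide in the primary chi-square test. The baseline period is important information for separating a pre-existing hospital difference from an effect of the intervention, and it should not carry a documentation artefact. Comparing the change at one hospital with the change at the other removes only shifts common to both, such as the due-date contact. The HITSystem 2.0 shift occurs at one hospital only and would remain.

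**Working it through.** **The plan's own figure.** The article gives no pre/post figure to reproduce. Its sample size does reproduce: 47% versus 20%, 80% power and two-sided 0.05 require 54 per hospital (108 in total) with a continuity correction, or 47 per hospital without. Sample size is not in question.

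**Sources by period, intervention hospital**

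| Component | Before go-live | After go-live |
|---|---|---|
| Antenatal visits | existing files and registers | HITSystem 2.0, back-filled and reviewed |
| Place of delivery | existing files and registers | HITSystem 2.0 plus due-date contact |
| Infant PCR | registers, possibly HITSystem 1.0 | HITSystem, linked to the mother |

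**Inputs**
- True complete retention π, unchanged between periods: 20% (the article's control assumption) and 30%. The article's stage rates multiply to 0.68 × 0.61 × 0.67 = 27.8%, which lies between them.
- Women after go-live: 54 (Power and Sample Size).
- Women before: 180, assumed from 10 × 18, the lower of the two monthly EID volumes times 18 months. This counts infants reaching EID rather than women entering PMTCT, so it is only a stand-in.
- Capture per component: c = 0.80 to 0.95 before and 0.99 after, independent across visits, delivery and infant test. These are assumptions; the article gives no capture rate.

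**Case A: all three components change capture.** Observed before = π × c³; observed after = π × 0.99³ = π × 0.970. Rejection rates are for the uncorrected chi-square test at two-sided 0.05, by exact enumeration of two binomials, 54 against 180.

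| π | c | Before | After | Spurious gain (points) | Rejects |
|---|---|---|---|---|---|
| 20% | 0.95 | 17.1% | 19.4% | 2.3 | 7.5% |
| 20% | 0.90 | 14.6% | 19.4% | 4.8 | 15.3% |
| 20% | 0.80 | 10.2% | 19.4% | 9.2 | 43.7% |
| 30% | 0.95 | 25.7% | 29.1% | 3.4 | 8.5% |
| 30% | 0.90 | 21.9% | 29.1% | 7.2 | 20.8% |
| 30% | 0.80 | 15.4% | 29.1% | 13.7 | 61.6% |

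With c = 0.99 in both periods the same calculation rejects 5.0% of the time, as it should.

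**Case B: infant testing at 99% in both periods.** Observed before = π × c² × 0.99.

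| c | Rejects, π = 20% | Rejects, π = 30% |
|---|---|---|
| 0.95 | 6.3% | 6.7% |
| 0.90 | 10.2% | 12.6% |
| 0.80 | 25.3% | 36.6% |

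**Sensitivity to the earlier sample (Case A, c = 0.90).** With 54 women before, the test rejects 10.1% (π = 20%) and 13.6% (π = 30%). With 324 (18 × 18, the higher EID volume), it rejects 16.8% and 22.6%.

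**How bad capture would have to be to matter fully.** For documentation alone to turn an observed 20% into the planned 47%, the earlier period would have to capture 0.20 / 0.47 = 42.6% of truly complete pairs relative to the later one. Over three components that is 0.426^(1/3), about 75% each.

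**The case against.** The strongest reply is that the article gives the pre/post comparison one clause and no test, and that a condensed article may leave abstraction rules to the full protocol. This stands in part: no inflated error rate can be attributed to a test the article has specified. But the article states both the comparison and the later-period source, and when it discusses data quality it names only the difference between sites. That is more than an omitted detail.

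The capture gap may also be small, since files and registers continue at both hospitals and HITSystem entries are back-filled from them. At 95% capture the inflation is slight.

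A reader might infer more than the documents support:

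- *That nothing was captured electronically before go-live.* The user-satisfaction paragraph refers to a current HITSystem 1.0, so infant tests may already have been electronic. Case B allows for this.
- *That the bias must favour the intervention.* The outcome requires all scheduled visits. Paper may leave a missed visit unrecorded, while HITSystem 2.0 flags late or missing services, so go-live could also lower measured retention. The model above allows records only to hide successes.
- *That the baseline period is the only check on hospital differences.* The hospitals are matched, and models will adjust for baseline covariates that differ significantly.
- *That all gain from the due-date contact is artefact.* The contact also encourages return to care, so part of any gain would be real, and it may apply at both hospitals.
- *That HITSystem and contact data should be discarded.* That would lose births at other health facilities known only from the contact.

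**Conclusion.** The point holds for the supporting pre/post comparison. Followed as written, the plan mixes a change in documentation with any change in care at the intervention hospital, and the stated limitation does not cover this. The likely direction favours the intervention, without certainty.

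The size cannot be derived from the article. Under the assumed capture rates and earlier sample, a nominal 5% test rejects about 7.5% to 62% of the time with no effect, or about 6% to 37% if only visits and delivery change capture. The upper ends need 80% capture per component and 30% true retention. A reader might take this as a flaw in the primary analysis. It is not: that test compares hospitals, and its documentation problem is a separate one that the Discussion already acknowledges. The comparison should be corrected, but the trial's main result does not depend on it.

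**What to change.** In Trial Design and Statistical Analyses, state that the main pre/post comparison, and any comparison of changes between hospitals, derives outcomes in both periods and at both hospitals from the same routine sources. These are the five already listed for the control site: mothers' medical records, the ANC registry, the pharmacy ART registry, the maternity registry and the HIV-exposed infant registry. Use one abstraction form and one mother-infant linkage rule throughout.

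For the 54 intervention women, report the outcome from those sources and, side by side, from HITSystem 2.0 plus due-date contact. The gap between the two shows how much of any gain is documentation. Extend the Discussion limitation to differences between periods.

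The cost is some added wording and paper abstraction for 54 women whose files and registers are kept in any case. The paper-only estimate may be conservative if paper recording declines once staff also enter data electronically; showing both results helps the reader judge that. The between-hospital primary test does not change.

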#### Study Sites and Setting

This study will be conducted in 2 government hospitals with similar provider-patient ratios and staffing structure, Kapsabet Hospital and Bungoma Hospital, both in western Kenya. Eligibility criteria for these hospitals include government funding; the current provision of PMTCT, EID, and ART services; at least one dedicated provider managing PMTCT services; and maintenance of individual-level patient files. Kapsabet Hospital serves a catchment area of approximately 91,000 people [43], has an average monthly EID volume of 10, and an average infant HIV transmission rate of 2.7% [44]. Bungoma Hospital serves a catchment area of approximately 92,412 people [43], has an average monthly EID volume of 18, and an average infant HIV transmission rate of 4.2% [44]. These hospitals serve less transient local populations, making them ideal pilot sites to adapt and modify the HITSystem 2.0 for the primary outcome of complete PMTCT retention.

#### Randomization

As a system-level intervention, it is neither feasible nor acceptable to randomize participation at the individual level. The hospital to receive the intervention will be determined by random assignment at the beginning of the study, using a random number generator program. The principal investigator and research staff will be blind to the process of assigning the sites.

#### Participant Eligibility

All HIV-positive pregnant women presenting for their first PMTCT appointment at the intervention and control site will be eligible for enrollment in the study. Women at the intervention site must also own or have reliable access to a mobile phone.

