#### Power and Sample Size

The required sample size was calculated to compare differences in proportions of complete PMTCT retention for the intervention (p1) and control (p2). We estimated complete retention by combining available retention data from Kenya for each phase: antenatal retention (68%) [19], hospital-based deliveries (61%) [36], and postnatal retention for HIV-exposed infants within 12 weeks (54.9% [21] to 80.7% [20]; average 67%). Recognizing that these estimates do not represent cumulative risk for the same individuals, we conservatively estimate complete PMTCT at the control site to be 20%. Our EID pilot data showed that retention doubled at 9 months with retention rates as high as 94.2% [33]. Using a midrange between differences achieved from published studies and our own pilot study, we conservatively estimate complete retention of 47% for HITSystem 2.0 participants. A sample size of 108 (54 intervention and 54 control participants) is needed to achieve 80% power to detect a significant difference in the proportion of complete PMTCT retention with chi-square tests (goodness of fit test: contingency table) with an effect size of 0.27 and a 2-tailed alpha of .05. Accounting for the proportion with mobile phone utilization, and 1.5% maternal mortality [45] and 3.7% [46] perinatal mortality, we estimate n=70 eligible participants. During Phase 3 enrollment, we plan to enroll n=54 of the n=70 eligible PMTCT patients per hospital. On the basis of our initial HITSystem pilot where <1% of women declined, we anticipate high participation.

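### Phone access is an entry condition at the intervention hospital only, so the primary comparison sets women with phones against all comers

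*Protocol article*

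**What the plan says.** Protocol article, Participant Eligibility, gives two rules in succession. The first covers both hospitals: "All HIV-positive pregnant women presenting for their first PMTCT appointment at the intervention and control site will be eligible for enrollment in the study". The second covers one: "Women at the intervention site must also own or have reliable access to a mobile phone". The article gives no reason for the difference.

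Power and Sample Size treats phone use differently. It arrives at the pool of available women this way: "Accounting for the proportion with mobile phone utilization, and 1.5% maternal mortality [45] and 3.7% [46] perinatal mortality, we estimate n=70 eligible participants". It then uses that same pool of 70 for each hospital, with 54 to be enrolled from it. The value of the phone share is not stated.

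Under Statistical Analyses, the primary outcome is compared between groups by chi-square test. Models are also to adjust for pre-intervention covariates that differ significantly; phone access is not named. The baseline survey items described under Procedures do not include it either. Mobile numbers are mentioned as part of the HITSystem 2.0 record, which exists only at the intervention hospital.

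**The concern.** Women without reliable phone access are removed from one arm by rule and kept in the other. Phone access may go with household resources, distance and ease of contact, and these could affect attendance, hospital delivery and return for infant testing, all of which are components of complete retention. Contact may also affect what is recorded: women who do not deliver at the study hospital are to be contacted to document the place of birth.

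If so, the control arm contains a subgroup with poorer recorded retention that has no counterpart in the intervention arm. Part of any observed difference would then reflect who was let in, not what the system did. The Discussion says the findings will shape a larger efficacy trial, so an inflated pilot effect could be carried into its planning.

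**Working it through.** **1. The plan's own sample size.** Inputs from Power and Sample Size: 47% against 20% complete retention, two-sided alpha 0.05, 80% power.

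- Two-proportion formula, pooled variance under the null: n = [1.96·√(2·0.335·0.665) + 0.842·√(0.47·0.53 + 0.20·0.80)]² / 0.27² = 46.8, so 47 per arm.
- With continuity correction: (46.8/4)·[1 + √(1 + 4/(46.8·0.27))]² = 53.9, so **54 per arm**, as stated.
- A 1-df chi-square with w = 0.27 also gives the stated total: (1.96 + 0.842)²/0.27² = 107.7, so 108.
- Power of the uncorrected test at 54 per arm is 85.5%.

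The sample-size arithmetic is sound. The issue is who is being compared.

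**2. Spurious difference when the intervention does nothing.** Let f be the share of women with phone access and r the ratio of retention with a phone to retention without one under usual care. The documents give neither, so both are assumed. Hold overall control retention at the planned 20%:

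- retention without a phone = 0.20 / (f·r + 1 − f)
- retention with a phone = r × that value
- spurious difference = retention with a phone − 0.20

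Example, f = 0.8 and r = 2: 0.20/1.8 = 11.1% without a phone, 22.2% with one, difference +2.2 points.

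| f | r | With phone | Without phone | Spurious difference | Chance of p < 0.05 with no effect |
|---|---|---|---|---|---|
| any | 1 | 20.0% | 20.0% | 0 | 5.0% |
| 0.9 | 1.5 | 20.7% | 13.8% | +0.7 points | 5.1% |
| 0.8 | 2 | 22.2% | 11.1% | +2.2 points | 5.9% |
| 0.7 | 2 | 23.5% | 11.8% | +3.5 points | 7.3% |
| 0.7 | 3 | 25.0% | 8.3% | +5.0 points | 9.5% |
| 0.6 | 3 | 27.3% | 9.1% | +7.3 points | 14.3% |

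The last column uses the uncorrected two-sided test at 54 per arm and treats the two hospitals as otherwise identical. The largest listed difference is 7.3/27 = 27% of the planned effect.

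**3. Power after restricting the control arm.** If 20% of control women lack a phone, 0.8 × 54 ≈ 43 remain. The same pooled formula, uncorrected, with 47% in the intervention arm gives:

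| Control retention among women with phones | 54 vs 54 | 54 vs 43 |
|---|---|---|
| 20% | 85% | 81% |
| 22% | 79% | 73% |
| 25% | 67% | 61% |

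Which row applies depends on whether the 20% control rate describes all comers or women with phones. The protocol does not say.

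**4. The two sections side by side.** The eligibility rule excludes women without phones at one hospital. The sample-size section discounts for phone use and reports one figure, 70, for both. A discount at both hospitals does not fit a criterion at one.

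**The case against.** The strongest reply is that direction and size are inferred. Nothing in the documents links phone access to retention, and reliable access is a broader test than ownership, so few women may be excluded; at 90% access and a ratio of 1.5 the difference is 0.7 points. This is also a pilot with one hospital per arm, where site is already fully confounded with intervention. All of that stands, and it limits the severity. It does not justify adding an avoidable difference in selection.

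Three stronger readings are tempting, and the documents do not support them.

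- A reader might infer that the comparison is certainly biased toward the intervention, on every secondary outcome too. The bias is zero if phone access does not predict retention, and outcomes such as viral-load turnaround depend partly on the laboratory.
- A reader might infer that the imbalance could not be adjusted for, because phone access is not a listed survey item. That list also omits education and HIV disclosure, which the analysis section uses, so absence from it does not show that the item is uncollected. Covariate adjustment alone would still find no counterparts for control women without phones; restriction would deal with them.
- A reader might take the phone discount as a second, contradictory eligibility rule. It is a planning count and may simply be cautious for the control hospital. It is an inconsistency to reconcile.

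**Conclusion.** The point holds. Followed as written, the plan compares women with phone access at one hospital with all women at the other, and nothing in the stated analysis restricts the comparison to like populations. Under the assumed ranges (phone access 60–90%, retention ratio 1.5–3, overall control retention 20%) the spurious difference is about 0.7 to 7 points in favour of the intervention. It is zero if retention does not differ by phone access. Differences of that size could not by themselves produce a 27-point effect, but they could inflate one, and they come on top of the site confounding. Severity: should-fix. The protocol's Results section reports enrolment under way and no between-arm outcome analysis done, so the change can still be made without knowledge of the results.

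**What to change.** - Apply the same phone criterion at both hospitals for remaining enrolment.
- Confirm whether phone access is recorded at the control hospital. If not, add it to the baseline survey for every control woman.
- Make the primary comparison among women with phone access at both hospitals, and report all control women as a sensitivity analysis.
- For control women already enrolled, take phone status only from records made at enrolment, such as contact details in the patient file. Later questioning would reach mainly women still in care and so select the population on retention. Show results with women of unknown status both included and excluded.
- Reconcile the phone discount behind the 70 eligible women with the eligibility rule, give the phone share used, and state which population the 20% control rate describes.

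The cost is one baseline item, some record abstraction, a smaller control group and the loss of nominal power shown above. That loss may be more than a few points: if control women with phones retain at 25%, power with 43 of them is about 61%. This is no reason to keep the mismatch, because the higher figure would then rest partly on control women of a kind excluded from the other arm.
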